
### Setting and recruitment

This multicenter trial involves four French centers: the Neurorehabilitation and the Maxillo-facial & Plastic Surgery departments at *Henri Mondor* University Hospitals, Créteil, the Maxillo-facial Surgery & Stomatology department at *Saint-Joseph* Hospital, Paris and the ENT, Stomatology & Head—Neck Surgery department at *Centre Hospitalier Intercommunal*, Creteil. Each of these centers admits > 20 cases/year of patients with unilateral peripheral facial paresis and should recruit over 20 participants in the study. A three-year period is planned for the study, each center starting the study once the total expected number of participants to be enrolled are lined up. Therefore, the objective is to run the protocol simultaneously for all participants of a given center.

### Procedures

This is a single-blind controlled trial, with randomization into two parallel groups, inclusion and randomization being computerized online (Cleanweb Telemedecine Technologies, France) in each investigator center. Clinical assessments, video recordings and 3D analyses of included subjects will be performed in a single investigating center: the Neurorehabilitation department at Henri Mondor University Hospitals, Créteil, France (evaluation center).

Screening visits will take place during regular clinic visits in each center. Participants meeting the selection criteria (see Table 1) will be invited to participate in the protocol. Written descriptive documentation will be provided and potential study subjects will be given at least two weeks to decide about participation. Informed consent will be signed and collected at D-30 of the study.

**Table 1 Tab1:** Inclusion and exclusion criteria

SELECTION CRITERIA
**Inclusion criteria:**
- Chronic and stable unilateral peripheral facial paresis, *i.e., more than* one year since the onset of the symptom, whatever its cause
- Age ≥ 18
- Outpatient
- Sufficient motivation level to participate in a 6-month facial rehabilitation program, based on the opinion of the investigator
- Signed consent
- Medically insured
**Exclusion criteria:**
- Evolving tumor causing the peripheral facial paresis
- Facial botulinum toxin injection less than six months before enrollment in the study, or planned during the study period
- Facial surgery less than two years before enrollment into the study or planned during the study period
- V-VII or XII-VII anastomosis or muscle transfer prior to enrollment into the study or planned during the study
- Nonsurgical aesthetic treatments – hyaluronic acid / lipofilling / laser / tensor thread – less than two years before enrollment in the study or planned during the study period
- Recurrent facial paresis
- Participation in another interventional research protocol on the face (aesthetic, rehabilitative, or surgical)
- Intercurrent disorder that could hinder the ability to participate in the rehabilitation program
- Preexisting cognitive, mental or psychological disorder preventing participation in the rehabilitation program or in the follow-up assessments, based on the opinion of the investigator
- Patient under legal protection

Randomization will be performed on inclusion day (D-30) by the chief investigator of each center, between the Conventional therapy group (CONV) and the Guided Self-rehabilitation Contract (GSC) group (see Randomization procedure below). Each participant will thus be randomly assigned to one of the two arms and will receive a rehabilitation program depending on the randomized arm, to be carried out over six months. In order to minimize any nocebo effect for the conventional treatment group, the study coordinator will not disclose details of the Guided Self-rehabilitation Contract to the physicians and physiotherapists who treat participants in the CONV group, nor to the CONV participants themselves.

Facial rehabilitation will begin the day after the first evaluation (D1).

In practice, two PM&R neurorehabilitation study physicians, a blinded assessor and an unblinded rehabilitation prescriber and coach, will separately meet each participant at D1, D90 and D180, for an assessment visit and a rehabilitation visit: 1) during the assessment visit, the blinded evaluator will run the clinical scales, self-questionnaires, and the 3D facial analysis (except for D90); 2) during the rehabilitation clinic visit, the unblinded PM&R physician will organize the rehabilitation. After receiving the result of the randomization at D-30, he/she will: 1) inform the participant on the arm that has been randomized; 2) teach the GSC, for those participants randomized in the GSC group; 3) find a community-based therapist through a dedicated listing, for those participants randomized in the CONV group; 4) give a rehabilitation booklet to the participant, according to the arm being randomized; 5) schedule the first visit (D1). Table 2 displays the study schedule.

**Table 2 Tab2:** Study schedule: enrolment, interventions and assessments

	**D-30**	**D1**	D30 ± 3 days	D60** ± **3 days	**D90 ± 2 weeks**	D120 ± 3 days	D150** ± **3 days	**D180 ± 2 weeks**
Signature of consent form	x							
Inclusion criteria checking	x							
Randomization	x							
Clinical examination	x	x			x			x
Teaching and then supervision of the guided self-rehabilitation contract (GSC group)		x			x			
Sunnybrook Facial Grading Scale	x	x			x			x
Créteil Scale		x			x			x
FaCE		x			x			x
FACE-Q		x			x			x
HADS		x			x			x
SF-12		x						x
3D facial motion analysis		x						x
Collection of adverse events					x			x
Phone calls			x	x		x	x	
Review of the diary (GSC group)					x			x

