#### Guided self-rehabilitation contract

In the GSC group, patients will be free to follow any conventional community-based therapy sessions, as in the CONV group. In addition, in the evaluation center, the study PM&R physician will provide three one-hour rehabilitation clinic visits at D1, D90 and D180, with the following objectives:*Explain the principles of the Guided Self-Rehabilitation Contract* to the patient. The GSC is a diary-based program centered on a moral contract in which each party, study participant and PM&R physician or GSC therapist, commits to the other on the following actions. The PM&R physician or GSC therapist commits to:*Prescribe* and *teach* a daily program of facial muscle strengthening exercises customized to the participant (see Figs. 1 and 2), and adjust the techniques according to clinical progress. Here, the study PM&R physician will provide a manual to the subject, which contains the prescribed program, with illustrations of the training exercises. Three facial muscle groups are targeted, selected because of the low risk of apraxia for the command to these muscles in the general population [33] and their localization (one for each third of the face): Frontalis, Orbicularis oculi and Zygomaticus. For each muscle group, the training program consists of three daily series of bilateral unassisted repeated efforts or movements of maximum amplitude until *fatigue* (e.g. 20 to 40 facial contractions per series, depending on fatigability). We have thus chosen to strengthen these three facial muscle groups that are crucial for facial motor function: raising eyebrows (expressiveness), closing eyes (eye protection) and smiling (communication, emotional expression, interaction with others). In practice, these muscles are easy to reach using voluntary command and therefore to rehabilitate. Each of them is located on one of the three vertical thirds of the face: during these efforts, several facial nerve branches covering the entire face are therefore stimulated from the top to the bottom of the face. Each branch of the facial nerve innervating several facial muscles, we postulate—and see in routine practice—that participants will also improve on neighboring muscles not directly targeted by the strengthening.*Request a diary* from the patient at each visit, in which the daily number of efforts or movements performed in each series in the interval between two visits with the PM&R physician should be recorded (Fig. 3). The PM&R physician stresses to the subject that such *self-monitoring* through the quantified written diary actually *belongs* to the therapy, in other words that the same physical exercises without maintaining the diary are likely to not carry the same efficacy [34–43]. Indeed, written feedback from patient to therapist/physician improves compliance to the self-rehabilitation program and thus the efficacy of this program [34–39]. Most importantly, the diary provides the patient with positive reinforcement, with potentially enhanced motor circuit excitability and even antidepressant effects [40–42, 44]. Regardless of self-monitoring, quantitative feedback on performance provided to the patient has been shown to improve rehabilitation effectiveness during the subacute phase of stroke [43].*Verify* patient compliance to the prescribed program by ensuring that the self-rehabilitation diary is well kept. The study physician will count the number of filled out days in the diary and divide it by the number of elapsed days since the last visit. In return, the subject commits to performing the prescribed daily self-rehabilitation program, including in particular the production of the written diary of exercises and to return it at each visit.

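### Procedures lists GSC teaching and the arm-specific booklet among actions before D1 is scheduled, whereas Table 2 and the Interventions section place GSC teaching at D1

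*Protocol article*

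**What the plan says.** The protocol article gives the timing of GSC teaching in several places.

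- **Procedures, paragraph before Table 2.** The duties of the unblinded physician are a numbered list: "After receiving the result of the randomization at D-30, he/she will: 1) inform the participant on the arm that has been randomized; 2) teach". What is taught is the GSC, to those allocated to it. Item 3 is finding a community therapist for CONV participants. The list closes with "4) give a rehabilitation booklet to the participant, according to the arm being randomized; 5) schedule the first visit (D1".
- **Same paragraph, one sentence earlier.** The blinded assessor and the unblinded physician "will separately meet each participant at D1, D90 and D180, for an assessment visit and a rehabilitation visit".
- **Table 2.** The row "Teaching and then supervision of the guided self-rehabilitation contract (GSC group" is marked at D1 and D90, and D-30 is empty. The row "Review of the diary (GSC group" is marked at D90 and D180.
- **Interventions, Guided self-rehabilitation contract.** The GSC arm receives "three one-hour rehabilitation clinic visits at D1, D90 and D180". Under the aims of those visits, "the study PM&R physician will provide a manual to the subject, which contains the prescribed program".
- **Procedures, just before the paragraph with the list.** "Facial rehabilitation will begin the day after the first evaluation (D1". No arm is excepted.

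Under Statistical analysis, the primary comparison is the change in the Sunnybrook composite score from D1 to D180, so D1 is the primary baseline.

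**The concern.** Conventional therapy needs a therapist and an appointment. GSC needs neither: once taught, a participant can do it alone. The moment of teaching therefore decides whether practice is possible before the baseline, and possible in one arm only.

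The Procedures list is the operational text that staff would follow, and its literal order puts teaching and the booklet in the month between D-30 and D1. Participants are selected for motivation (Table 1). If some began exercising early, their D1 score would no longer be a pre-treatment value, and the D1 to D180 change would measure something different in the two arms. The Statistical analysis section also allows for baseline adjustment when the groups differ at baseline despite randomisation. A difference caused by early practice would not be a chance imbalance, although that adjustment would treat it as one.

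**Working it through.** **1. Does the list fall before D1?** Item 5 (schedule D1) can only happen before D1. Item 3 (find a CONV therapist) must also precede D1, because the Research design section gives that search as the reason for the one-month gap. The list is tied to receipt of the D-30 result. Items 2 and 4 (teaching, booklet) sit between items that must precede D1. The literal reading is pre-D1.

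**2. What do the other places say?**

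| Place | GSC teaching |
|---|---|
| Procedures, numbered list | after the D-30 result, before D1 is scheduled |
| Procedures, visit days in the same paragraph | physician meets participants at D1, D90, D180 |
| Table 2 | D1 and D90; D-30 empty |
| Interventions, GSC subsection | visits at D1, D90, D180 |

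One place conflicts with three. The three agree with each other and with the stated start of rehabilitation, so D1 is clearly the intended day.

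**3. Is the start of rehabilitation also contradictory?** No. Procedures gives one start, the day after the D1 evaluation. The Research design section also refers to onset at D1, for the CONV group. No text says that GSC exercise begins earlier.

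**4. How much practice would early teaching make possible?** The GSC subsection prescribes 3 muscle groups, 3 daily series each, with 20 to 40 contractions per series as its example.

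- Per day: 3 × 3 × 20 = 180, to 3 × 3 × 40 = 360.
- Over 30 days: 180 × 30 = 5,400, to 360 × 30 = 10,800.

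This is a ceiling on exposure. It assumes teaching at D-30 and full daily practice contrary to the stated start. It is not an effect size.

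**5. What would that do to the primary contrast?** Let g(m) be the mean gain attributable to GSC after m months of practice, with g(0) = 0.

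- Start at D1: the D1 to D180 change contains g(6).
- Start at D-30: it contains g(7) − g(1).
- Loss = g(6) − [g(7) − g(1)] = g(1) − [g(7) − g(6)], the first month's gain minus the seventh month's.

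With the planned difference of 20 − 10 = 10 points (Sample size section) and linear accrual, the gain is 10/6 = 1.67 points a month. The advantage is then 1.67 at D1 and 7 × 1.67 = 11.67 at D180, and the difference is still 10. The loss is zero. If gains are front-loaded or plateau, the first month exceeds the seventh and the contrast shrinks. If early practice lowered the D1 score, g(1) would be negative and the contrast could grow. The article gives no curve for g, so the loss cannot be expressed in points.

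**The case against.** The best defence is that the intent is plain. The list follows a sentence placing this physician's visits at D1, D90 and D180, and leads into Table 2, which leaves D-30 empty for teaching. It can be read as a loose list of duties, with the schedule governing the dates. That largely stands as to intent. It does not rescue the wording, because the list is numbered, tied to D-30 and ends by scheduling D1.

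Several stronger readings are tempting, and the document does not support them.

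- **That the start of the programme is given in two incompatible ways.** It is given once, the day after the D1 evaluation. Only the delivery of teaching and booklet conflicts.
- **That nothing restrains early practice.** The stated start does. What is absent is an instruction to hold back teaching and material until D1.
- **That the booklet is the GSC manual.** The booklet goes to both arms, and the article never says that it is the manual described in the GSC subsection.
- **That the bias could only hide a benefit.** The Sunnybrook composite includes synkinesis, and the Background reports a longstanding fear, which the authors dispute, that strengthening provokes overactivity. A lower D1 score after early practice cannot be ruled out from the document.
- **That a loss of power can be quoted.** Any such figure needs an assumed loss in points, for which the article gives no basis.
- **That participants were taught early.** Trial status reports 33 of 82 included by December 2022, and the document does not show which timing was used for them.

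**Conclusion.** The point holds as an inconsistency in an operational instruction. The Procedures list puts GSC teaching and the arm-specific booklet before D1, and Table 2, the GSC subsection and the physician's own visit days put teaching at D1. Harm requires three things together: staff follow the list, participants practise before the stated start, and the first month's gain differs from the seventh's. If gains are front-loaded or plateau, the primary contrast is biased against GSC, which is the likelier direction but not the only possible one. The size is unknown, and nil if the stated start is respected. The severity is minor. It still deserves correction because a distorted baseline cannot be repaired afterwards, and 82 − 33 = 49 participants remained to be enrolled at the December 2022 count.

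**What to change.** In the Procedures list, limit the D-30 actions to informing the participant of the arm, finding a CONV therapist and scheduling D1. Add that GSC teaching and any GSC programme material are given at D1, only after the blinded baseline assessment is complete. This matches Table 2, the GSC subsection and the stated start of rehabilitation.

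Optionally, record the date of first GSC teaching for each GSC participant, including those already enrolled, so that the timing can be shown.

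The cost is a one-sentence clarification and, if wanted, one date field. No visit is added and the primary analysis stays as planned.

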### Research design

VISAGE is a single-blind, prospective, controlled, randomized multicenter study in 82 participants with chronic unilateral peripheral facial paresis (> 1 year since facial nerve injury). The trial will be run in four tertiary centers, including maxillofacial surgery (2), otolaryngology (1) and neurorehabilitation (1) units. For all participants, the study will begin at inclusion (Day-30). At that time point, the investigator will implement computerized randomization to assign a group treatment to the patient, between Guided Self-rehabilitation Contract (GSC) and conventional therapy (CONV) alone, for six months. A delay of one month between inclusion (D-30) and the first assessment (D1) is anticipated to account for the time to find a therapist and to ensure timely rehabilitation onset (D1) for the participants in the CONV group. In the GSC group, the participants will be free to continue potential preexistent conventional therapy if there was any. The total duration of subject participation in the study is seven months. Study data will be analyzed through intention-to-treat and per-protocol analyses.

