### Interventions

#### Conventional therapy

In the Conventional Physical Therapy group (CONV), the study PM&R specialist prescribes physiotherapy and/or speech therapy sessions at inclusion (D-30), for a six-month period starting at D1. For this purpose, a list of physical and speech therapists specialized in PFP rehabilitation and working in the Greater Paris area is provided to each subject. Each therapist of that list has personally agreed to potentially take care of patients of the VISAGE study in due course. Such community-based therapy sessions are universally and indefinitely covered by public health insurance in France. Whichever the study group, subjects already undergoing community-based rehabilitation are free to pursue that rehabilitation during the six months of the study. Indeed, the discontinuation of previous rehabilitation might lead to nocebo effects, which is well known in rehabilitation RCT studies [31, 32]. The treatment of the control group is intended to reflect the usual management of patients with chronic peripheral facial paresis. The physiotherapists caring for the patients in the control group are all trained in the rehabilitation of facial paresis and accustomed to treating this disorder. As mentioned above, there is no standardized rehabilitation protocol and the techniques are diverse and heterogeneous among therapists. Each practitioner in the control group therefore chooses the frequency of the rehabilitation sessions, the techniques used and the duration of each rehabilitation session. Such information will be noted however, by the study examiners to quantify and qualify the control group rehabilitation.

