#### Statistical analysis

Descriptive statistical analysis will be carried out to evaluate randomization groups in terms of demographic, and initial clinical and kinematic characteristics, including PFP cause, delay since injury, side of paresis, previous drug treatments, and comorbidities. Quantitative data will be described using means (± SD) or medians (with IQR), depending on the normality of distributions, and qualitative data will be reported as numbers or percentages.

Changes in the Sunnybrook Composite score between D1 and D180 will be evaluated by Student’s *t* test. No interim analysis has been planned. The primary outcome analysis will be performed using Intention to treat (ITT) analysis. Comparative analysis of quantitative values at J90 and J180 – including primary and secondary outcomes—will be performed with Student’s *t* tests for independent samples or with Mann–Whitney non-parametric tests, depending on conditions. Changes in quantitative values from inclusion to each assessment visit (D90-D1, D180-D1) will be compared taking into account the baseline data in case of baseline intergroup differences despite randomization. Within-group changes will be tested through Student’s *t*-tests for matched data or Wilcoxon Rank sum tests, depending on the conditions. Multiple linear regression models will be tested to identify independent predictors associated with the changes in quantitative parameters over time, including longitudinal analysis of random effects (mixed models).

Comparative analysis of binary parameters will be run through Chi-square or Fisher’s exact tests, depending on conditions. Multivariable analysis will be generated through logistic regression models. Intra- and inter-rater reliability studies will use frequencies of agreement, intraclass correlation coefficients, Cohen and Fleiss kappa coefficients and coefficients of variation. Spearman or Pearson coefficients will be calculated between scores on the various scales, depending on conditions. Complementary analyses on the primary outcome and all analyses regarding secondary outcomes will be performed in both ITT and per protocol (PP) populations to describe the excluded patients of the PP population and to evaluate the robustness of the results.

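### FaCE, FACE-Q, HADS and SF-12 have no baseline taken before participants learn their arm, so change from D1 on these self-rated outcomes is open to influence by knowledge of the allocation

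*Protocol article*

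**What the plan says.** The order of events comes from four places in the protocol article.

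- **Randomisation.** Procedures: "Randomization will be performed on inclusion day (D-30) by the chief investigator of each center".
- **Disclosure.** Also in Procedures, once the D-30 result is received, the unblinded physician's first step is to "inform the participant on the arm that has been randomized". The last step of the same list is "5) schedule the first visit (D1"), so disclosure comes before D1.
- **The gap.** Research design: "A delay of one month between inclusion (D-30) and the first assessment (D1) is anticipated to account for the time to find a therapist". The Conventional therapy section adds that the study physician "prescribes physiotherapy and/or speech therapy sessions at inclusion (D-30), for a six-month period starting at D1". CONV participants must therefore know their arm from about D-30.
- **Measurement.** In Table 2, FaCE, FACE-Q and HADS are marked at D1, D90 and D180, and SF-12 at D1 and D180. None is marked at D-30. The Sunnybrook scale is the only outcome scale marked there.

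Statistical analysis defines change as "Changes in quantitative values from inclusion to each assessment visit (D90-D1, D180-D1"), compared with account taken of baseline if the groups differ there. The same section separately plans a between-arm comparison of the D90 and D180 values themselves, for primary and secondary outcomes.

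**The concern.** These four instruments carry secondary objectives i to iv: disease-specific quality of life, general quality of life, aesthetics and mood. The participant is the rater, so the blinded assessor who administers the forms gives no protection. By D1 each participant has known for about a month whether to expect the new programme or usual therapy.

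The protocol itself takes this kind of reaction seriously. It withholds details of the experimental programme from CONV participants "In order to minimize any nocebo effect for the conventional treatment group". If hope or disappointment moves the D1 answers, the shift is subtracted out of every D1-based change.

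The provision to account for baseline differences does not solve this. It treats a D1 difference as chance imbalance despite randomisation. Here D1 comes after randomisation and disclosure, so a difference could itself be an effect of allocation. No earlier patient-reported value exists to tell the two apart. The text also describes these as changes from inclusion, although inclusion is D-30. The formula makes D1 the reference, so that is loose wording, but it hides the fact that the baseline is post-randomisation.

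**Working it through.** **Number per arm.** Sample size gives a difference of 20 − 10 = 10 points, SD 13, two-sided 5% and 90% power. The normal approximation is n = 2 × (1.960 + 1.282)² × 13² / 10² = 35.5, so 36 per arm, as stated. Allowing 10% loss gives 36 / 0.9 = 40, against 41 stated, which is close enough. The sample size is not in dispute. I use 36 per arm below and assume the same number for the questionnaires.

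**How a D1 shift travels.** Let s be the between-arm shift at D1 caused by knowing the arm, f the fraction still present at D180, and b the within-arm slope of D180 on D1.

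| Analysis at D180 | Contribution of the shift | Fades fully (f = 0) | Persists fully (f = 1) |
|---|---|---|---|
| D180 − D1 | fs − s = −(1 − f)s | −s | 0 |
| D180 adjusted for D1 | (f − b)s | −bs | (1 − b)s |
| D180 compared directly | fs | 0 | s |
| D180 − (D-30) | fs | 0 | s |

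The D1 value itself enters only the first two rows. In the last two, only what remains in the D180 answers counts. The last two rows also estimate the same between-arm difference, whereas change from D1 does not.

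**Size, on assumed values.** The documents give no size for s, so I take 0.1 to 0.3 SD of the score with full fading. The SD of a change is SD × √(2(1 − r)), where r is the D1-D180 correlation, also not stated. At r = 0.5 it equals the SD of the score, so the standard error of the difference in change is √(2/36) = 0.236 SD.

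| Assumed shift | In standard errors (r = 0.5) | Rejection rate, two-sided 5% test on D180 − D1, no true D180 difference |
|---|---|---|
| 0.1 SD | 0.1 / 0.236 = 0.42 | about 7% |
| 0.2 SD | 0.2 / 0.236 = 0.85 | about 14% |
| 0.3 SD | 0.3 / 0.236 = 1.27 | about 25% |

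The rate is 1 − Φ(1.96 − s/SE) + Φ(−1.96 − s/SE).

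**Sensitivity to r, for the 0.2 SD shift.**
- r = 0.3: SE = 0.236 × √1.4 = 0.279, ratio 0.72.
- r = 0.7: SE = 0.236 × √0.6 = 0.183, ratio about 1.1.

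**The case against.** The other side has several good arguments.

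1. **A planned analysis escapes the problem.** Comparing D90 and D180 scores between arms does not use D1. This stands. A reader might infer that every between-arm result on objectives i to iv is biased; the documents do not support that. Only change-based and D1-adjusted analyses are exposed.
2. **No shift is shown.** This stands too. A reader might infer that the D1 scores are already distorted, but the documents establish only the opportunity. They give no occurrence, size or direction, and withholding programme details from CONV participants is a partial safeguard.
3. **The illustration is an extreme case.** Full fading on raw change gives the largest effect. If the shift persists it cancels from D180 − D1, and under regression adjustment it is multiplied by the slope. This stands, so the figures show scale only.
4. **A D-30 baseline does not blind the participants.** They still self-report at D90 and D180 knowing their arm, and D180 minus D-30 carries any lasting expectation in full. True, but so does the direct comparison. The earlier baseline does not claim to remove follow-up reporting bias; it stops the baseline from adding its own.
5. **D1 is a reasoned choice.** It is the last value before rehabilitation starts, and assessments are centralised in one evaluation centre. That justifies keeping D1 for rated and 3D measures. It is weaker for self-completed forms, which need no trained rater or equipment, in a condition required to be stable.

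The point also should not be stretched to the primary outcome. The Sunnybrook change does start at D1, but a blinded assessor scores it and a D-30 value exists.

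**Conclusion.** The concern holds in a limited form. The timing is clear from the text: no FaCE, FACE-Q, HADS or SF-12 value precedes knowledge of the arm, and the defined change scores use that post-disclosure value. The changes on secondary objectives i to iv, and any analysis adjusted for D1, are therefore open to an allocation effect at baseline that cannot be separated from chance imbalance.

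The size is unknown. About 0.4 to 1.3 standard errors is an illustration that assumes a 0.1 to 0.3 SD shift, full fading by D180, a correlation of 0.5 and 36 analysed per arm. The month is the planned gap; the exact disclosure day is not dated, only placed before D1 is scheduled. The direct D90 and D180 comparisons are not affected by a D1 shift, and neither the primary analysis nor the sample size is called into question. This is a modest weakness in secondary analyses that is cheap to remove for future participants.

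**What to change.** - In Table 2, add FaCE, FACE-Q, HADS and SF-12 at D-30, completed after consent and before randomisation.
- In Statistical analysis, name the D-30 value as baseline for secondary objectives i to iv, whether for change or as a covariate. Keep D1 as descriptive, and correct the wording so that changes described as from inclusion do start at D-30.
- For participants already randomised without a D-30 value, do not substitute D1, which would mix two baseline definitions. Rely on the already planned between-arm comparison of D90 and D180 scores without conditioning on D1. Report D1-based change as a sensitivity analysis labelled as using a post-disclosure baseline.

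**Cost.** A small amendment and 15 + 10 + 14 + 12 = 51 items at a visit that already takes place. The burden falls on the recruiting centres rather than only on the evaluation centre. Trial status reports 33 of 82 included by December 2022. From that count, 82 − 33 = 49 participants (60%) could have had a clean baseline. Those already randomised cannot be corrected, so the benefit shrinks with delay.
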